### Participant eligibility

#### Inclusion criteria

The following are inclusion criteria for the study: a) be aged between 15 and 25, b) have suicidal ideation as detected when 2 or more from 5 categorical questions about suicidal ideation are affirmatively reported in the Columbia Suicide History Form (C-SSRS) [40], c) a score of ≥38 out of 84 on the Exploratory Questionnaire of Personality-III-BPD (CEPER-III-BPD) [41] and d) sufficiently proficient in Spanish to undergo treatment.

#### Exclusion criteria

Exclusion criteria includes the following: a) antisocial personality disorder as measured in the Clinical Interview for DSM-IV Axis II Disorders (SCID-II) [42], b) substance/alcohol abuse or dependence to the point that the therapist suspects it may interfere with their adherence to treatment, c) high suicidal risk as detected when suicidal ideation intensity is 4 or more over a 5-point scale as assessed by the C-SSRS [40] and d) a score of ≥35 out of 60 points on the Credibility/Expectancy Questionnaire (CEQ) [43], with the aim of considering if the subject expects to improve with treatment.

Efforts to reduce dropout rates will be made by providing support for travel arrangements and sending text message reminders to boost attendance. All participants will sign an informed consent form prior to inclusion in the study (parents must sign on behalf of participants under the age of 18). The study will follow the principles of Good Clinical Practice and the Declaration of Helsinki.

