## Methods

### Study design

The study is planned as a 12-month pragmatic, two-armed parallel randomised controlled trial (RCT). It will randomise 72 young subjects (aged between 15 and 25) with suicidal ideation and/or self-injuring behaviour and borderline personality traits. Participants will be randomly assigned to one of two groups, Iconic Therapy or Structured Support Therapy, on a 1:1 basis to form 4 groups of 18 patients. Two of these groups will be included in the Iconic Therapy group and the other two in the Structured Support Therapy group. A total of 8 volunteer psychologists will administer the therapies formed into 4 pairs of therapists and co-therapists. The volunteer psychologists are required to have obtained a Master’s Degree in Psychology and have previous experience with patients. It is inherently not possible to blind psychologists delivering the Iconic Therapy intervention, since they have been specifically trained for 10 months. The goal of the psychologists conducting the control group is to obtain good clinical results. They will achieve this through therapeutic intervention.

Primary and secondary outcome measures will be assessed at baseline, after treatment (10–12 weekly sessions) and at 12-month follow-up (15 months after the baseline). Study variables and assessment times are shown in Table 1.

**Table 1 Tab1:** Study variables and assessment time

Instrument	Assessment area	Time of assessment
Primary outcomes		
BSL-23^a^	BPD symptoms severity	Baseline After treatment At 12 months
Secondary outcomes		
C-SSRS^b^	Suicidal ideation or behaviour	Baseline After treatment At 12 months
DSM-V criteria^c^	Non-suicidal self-injury diagnosis	Baseline After treatment At 12 months
CSRI^d^	Economic evaluation	Baseline At 12 months
Subsidiary measures		
IG^e^	Daily life adjustment	Baseline After treatment At 12 months
CEQ^f^	Credibility/expectancy questionnaire	After treatment At 12 months
Ad hoc scales^g^	Perceived subjective global improvement *(self-reported)*	After treatment At 12 months
Ad hoc scales^h^	Perceived global improvement *(family/friends reported)*	After treatment At 12 months

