##### Credibility/expectancy questionnaire

Satisfaction with treatment is assessed by the CEQ [43]. It is a brief 6-item questionnaire covering how logical the treatment seemed, the extent of patient satisfaction, whether other psychological problems could benefit from it, its usefulness for the patient’s specific problem and to what extent the treatment was aversive, rated on a scale from 0 (not at all) to 10 (very strong). This instrument has demonstrated high internal consistency (α = .79 for expectancy and α = .81 for credibility) and good test-retest reliability (*r* = .82 for expectancy and *r* = .75 for credibility) [49]. The questionnaire is delivered post-treatment and at 15 months after the baseline.

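### As written, the CEQ exclusion removes the high end of the expectancy scale, against its stated aim and with no pre-treatment CEQ scheduled; separately, the ideation criterion is narrower than the declared population.

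*Protocol article*

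**What the plan says.** **CEQ rule.** The Exclusion criteria section of the protocol article lists, as item d, "a score of ≥35 out of 60 points on the Credibility/Expectancy Questionnaire (CEQ"), "with the aim of considering if the subject expects to improve with treatment".

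**CEQ content and scoring.** The section on the Credibility/expectancy questionnaire presents it as the measure of satisfaction with treatment: "It is a brief 6-item questionnaire covering how logical the treatment seemed, the extent of patient satisfaction", among other topics, with each item "rated on a scale from 0 (not at all) to 10 (very strong").

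**CEQ timing.** The same section states: "The questionnaire is delivered post-treatment and at 15 months after the baseline". In Table 1 (Study design), the row for the "Credibility/expectancy questionnaire" shows two assessment times, after treatment and at 12 months, and no baseline entry. The Screening assessment section names the C-SSRS, the CEPER-III-BPD and the BSL-23.

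**Population.** Study design describes young people "with suicidal ideation and/or self-injuring behaviour and borderline personality traits", and the Abstract (Methods/Design) says much the same. Inclusion criterion b requires that patients "have suicidal ideation as detected when 2 or more from 5 categorical questions about suicidal ideation are affirmatively reported" on the C-SSRS. It is joined to the other criteria by a plain conjunction, and no self-injury alternative is offered.

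**The concern.** A rule meant to check whether a patient expects to improve would be expected to keep those who do. Placed under exclusion with a greater-than-or-equal sign, it does the reverse. Setting and recruitment says that referring clinicians will work from eligibility forms, so an inverted criterion could be copied straight into practice.

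The second difficulty is that the instrument is described, in both text and table, as given only once treatment is over, and some of its items ask about a treatment already received. A recruiting clinician has no scheduled score to which the rule could be applied.

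The third is a mismatch between the population announced and the population admitted. The Background rests much of its rationale on early intervention for self-injury, and non-suicidal self-injury diagnosis is a secondary outcome. Yet one of the groups that the and/or wording promises to include cannot enter.

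What is at stake is who is enrolled, whether eligibility can be applied consistently, and to whom the results can be said to apply.

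**Working it through.** **1. Reproduce the CEQ maximum.** Inputs: 6 items, top item score 10 (Credibility/expectancy questionnaire section). Maximum = 6 × 10 = 60, which matches the figure of 60 in the Exclusion criteria. Both sections therefore refer to the same total score.

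**2. Locate the cut-off.**
- Share of the maximum: 35 / 60 = 58.3%.
- Mean item score at the cut: 35 / 6 = 5.83.
- Highest eligible total: 34, a mean item score of 34 / 6 = 5.67.
- Scale midpoint: 60 / 2 = 30, which is below the cut and so eligible.

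The rule excludes totals 35 to 60 and admits totals 0 to 34.

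**3. Check the direction of the scale.** The article does not say outright that a high total is favourable. The anchors run from not at all to very strong, and the topics listed are logic, satisfaction, value for other problems, usefulness and aversiveness. Only aversiveness could run the other way. Suppose it is not reverse-scored:
- One such item: a wholly favourable patient scores 5 × 10 + 0 = 50 and is excluded; a wholly unfavourable one scores 0 + 10 = 10 and is admitted.
- Two such items (five topics are listed for six items, so this is the worst case): the totals are 4 × 10 + 0 = 40, excluded, and 0 + 20 = 20, admitted.

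The direction survives either way: the rule removes the favourable end.

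**4. Set the CEQ timing statements side by side.**

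| Place in the article | When the CEQ is used |
|---|---|
| Exclusion criteria | To decide entry, hence before randomisation |
| Credibility/expectancy questionnaire | After treatment and 15 months after baseline |
| Table 1 | After treatment and at 12 months |
| Screening assessment | Not named |

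The last two times agree with each other, because Study design places the 12-month follow-up at 15 months after baseline. Neither is before treatment. By contrast, the C-SSRS and BSL-23, both used at screening, do have a baseline entry in Table 1.

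**5. Set the population statements side by side.**

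| Patient | Fits Study design wording | Meets inclusion criterion b |
|---|---|---|
| At least 2 ideation items, no self-injury | Yes | Yes |
| At least 2 ideation items, with self-injury | Yes | Yes |
| Fewer than 2 ideation items, with self-injury | Yes | No |

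The mismatch is confined to the third row.

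**The case against.** **The CEQ rule is probably a slip.** An inclusion threshold printed in the wrong list is the likeliest explanation, and the stated aim does not say in so many words that high scorers should be kept. That is fair, and the article cannot settle it. But it offers no rationale for removing patients with high expectancy, and a slip in an eligibility rule still needs correcting.

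**Absence from a schedule proves little.** Table 1 covers outcome measures and also omits the CEPER-III-BPD and SCID-II, both eligibility tools; Screening assessment omits SCID-II as well. So silence there is weak evidence, and a condensed article may leave out a screening form. What stands is the positive statement in the questionnaire's own section that it is given after treatment and at 15 months, with Table 1 repeating those two times. Nor are all items unanswerable beforehand: logic and usefulness can be rated once a programme has been described, and the article reports a separate expectancy component. Satisfaction and aversiveness are the clearly retrospective ones.

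**Stronger readings that the article does not support.**
- A reader might infer that only patients who doubt the treatment could enter. Totals up to 34 include the midpoint and moderate expectancy.
- A reader might infer that most motivated patients would be screened out. No CEQ distribution is given, so the proportion lost is unknown.
- A reader might infer that the rule will be applied after treatment and so undermine the intention-to-treat analysis. The rule sits under Participant eligibility, nothing proposes a later use, and Data analyses commits to intention to treat.
- A reader might infer an ideation-only sample. Self-injurers who also meet the ideation threshold remain eligible.

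**Conclusion.** The point holds as three inconsistencies in the text.

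1. The CEQ exclusion runs against its stated aim. Followed literally, it restricts the sample to totals of 0 to 34 out of 60. This rests on higher totals being favourable, which the anchors and topics support even if aversiveness is not reverse-scored.
2. Its use for eligibility contradicts the article's own schedule for the questionnaire, and some items as described presuppose treatment.
3. The declared population is wider than inclusion criterion b by one group: self-injurers who affirm fewer than two of the five ideation questions.

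A criterion applied before randomisation falls on both arms alike. The consequence is for who is recruited and for generalisability; the between-arm comparison is not biased by it. The article gives no data from which to estimate how many patients either rule would turn away, so the size can be stated only as the part of the scale, and the group, removed.

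**What to change.** - **CEQ direction.** Reconcile item d of the Exclusion criteria with its stated aim, or delete it. If high expectancy really is to be excluded, give the reason.
- **CEQ timing.** If the criterion stays, show a pre-randomisation administration in Table 1 and in the Credibility/expectancy questionnaire section, with items worded prospectively.
- **Population.** Reconcile the Abstract and Study design with inclusion criterion b, either by adding a self-injury route to the criterion or by narrowing the stated population. The choice belongs to the sponsor.
- **Forms.** Check the eligibility forms given to recruiting clinicians against the reconciled text.

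The cost is an amendment to the eligibility wording and, if the CEQ rule is kept, one six-item form at screening. If recruitment has already begun, the report should also state which direction of the CEQ rule, and which ideation or self-injury rule, was actually applied.

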#### Setting and recruitment

Sample recruitment will take place at the Regional University Hospital of Málaga (Spain). This is a public mental health service with a catchment area of approximately 300,000 inhabitants. Psychologists and psychiatrists there will be given eligibility forms and will recruit outpatients until the required sample is filled.

### Study procedure

#### Screening assessment

Suicidal risk will be assessed by use of the C-SSRS [40]. Borderline personality or coexisting behavioural trends will also be measured with the CEPER-III-BPD [41]. Symptom severity will be measured through the BSL-23 [44].

#### Randomisation

Once grouped by age, the principal investigator will randomise patients into either the Iconic Therapy group or Structured Support Therapy group on a 1:1 basis.

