
Notes. ^a^All patients are free to contact the principal investigator throughout the process to solve practical questions about the use of session contents. ^b^10–12 group sessions given by 2 specifically trained psychologists using the guideline draft. ^c^11 group sessions given by 2 psychologists using a non-manualized program

A total of 3 more group sessions (2 of them matched with the assessment) will be delivered by the therapist and co-therapist after treatment and at 6 and at 12 months follow-up as well as an undetermined number of face-to-face sessions with the principal investigator. The same is true for the Structured Support Therapy group. These sessions are aimed to assure participants’ needs are met and to minimise dropout rates in both groups. Nevertheless, the Iconic Therapy group will continue to see and reinforce visual images, whereas those in the control group will receive plain verbal explanations without illustrations.

As this is the first time the Iconic Therapy programme is being delivered by therapists other than its creator or principal investigator, group sessions will be supervised from behind a unidirectional window by the principal investigator. Also, two Iconic Therapy randomised group sessions will be recorded by the creator for analysis. During the 10–12 week period of the study, supervision and feedback will be given to the therapist and co-therapist of both study groups.

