#### Data analyses

Patients will be included in intent-to-treat analyses. Participants’ demographic characteristics will be summarised using descriptive statistics, and the comparability of the treatment groups will be examined using *χ*^2^ tests for categorical variables and *t* tests for continuous variables.

Data analyses of the primary and secondary outcomes will be conducted using generalised estimating equation (GEE) models. Essentially, GEE models extend generalised linear models (GLMs) to allow analysis of repeated measurements or other correlated observations. The response can be scale, counts, binary or events-in-trials. In addition, GEE models can also deal with data that have missing values as long as the missing value is completely random. Parameter estimation can still yield robust results [51].

In these GEE models, treatment conditions (experimental vs. control) will be included as the between-subjects factor and time (baseline, after treatment and at 12 month follow-up) as the repeated measure. Main effects and interaction between treatment and time will be examined. When the interaction effect is statistically significant, simple main effects analyses will be conducted.

IBM SPSS (version 22.0 for Windows) will be used for the statistical data analyses. Statistical significance will be defined as *p* < .05. Bonferroni correction will be applied for post hoc multiple comparisons.

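### The principal investigator, who also observes the therapy sessions and sees participants individually, performs the randomisation, and no concealment safeguard is described

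*Protocol article*

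**What the plan says.** The Randomisation section is one sentence and names the allocator: "Once grouped by age, the principal investigator will randomise patients into either the Iconic Therapy group or Structured Support Therapy group", in a 1:1 ratio. It does not say how the sequence is produced, who holds it, or when an assignment is revealed.

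The Iconic therapy group section gives the same person three further links to the treatments:

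- Observation of sessions: "group sessions will be supervised from behind a unidirectional window by the principal investigator".
- Direct contact with participants: "an undetermined number of face-to-face sessions with the principal investigator". The next sentence extends this to the control arm, and note a to Table 2 lets every patient contact the principal investigator throughout.
- A history with the experimental therapy: "this is the first time the Iconic Therapy programme is being delivered by therapists other than its creator or principal investigator".

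The section also says that "supervision and feedback will be given to the therapist and co-therapist of both study groups", without naming who gives the feedback.

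Under Setting and recruitment, identifying and enrolling patients falls to psychologists and psychiatrists of the hospital service. The principal investigator is not named there.

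**The concern.** Randomisation protects a comparison only if the person who assigns patients cannot choose, foresee or revise the assignment in the light of who the patient is. The usual way to secure this is to separate the person who controls the sequence from those with a role in treatment. Here the article joins the two roles. The allocator has a background in one of the therapies, watches it being delivered, and has personal contact with participants.

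The stake is selection bias: patients expected to respond well could end up more often in one arm, by intent or not. The trial has few later defences. The Study design section says that the psychologists delivering Iconic Therapy cannot be blinded, and the BSL-23 is completed by the patient. With 72 patients planned, a handful of placements is a visible share of each arm. An article may leave block sizes or envelope procedures to the full protocol. Naming the allocator is different: it is a choice that the article makes, and it makes it in favour of a person who is not independent.

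**Working it through.** No figure in the plan bears on this point, so the check sets the statements side by side.

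| Question | What the article gives | Section |
|---|---|---|
| Who allocates? | The principal investigator | Randomisation |
| Who recruits? | Hospital psychologists and psychiatrists | Setting and recruitment |
| Who observes sessions? | The principal investigator | Iconic therapy group |
| Who holds individual sessions, both arms? | The principal investigator, number not fixed | Iconic therapy group |
| Who had delivered Iconic Therapy before? | Its creator or the principal investigator, by implication | Iconic therapy group |
| Who generates or holds the sequence? | Not stated | – |
| When is an assignment revealed? | Not stated | – |
| Are the therapists blinded? | Not possible for Iconic Therapy | Study design |
| How is the primary outcome obtained? | Self-rated BSL-23 | Primary outcome measure |

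**Step 1: independence.** Rows 1, 3, 4 and 5 concern one person. The allocator is not independent of the treatments. This follows from the text without inference about conduct.

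**Step 2: concealment.** Rows 6 and 7 are empty. Row 2 separates recruitment from allocation, which limits steering of who is enrolled. It does not limit which arm an enrolled patient is placed in, because that step stays with the principal investigator.

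**Step 3: timing.** The individual sessions and the observation of groups belong to treatment and follow-up. They show involvement with the treatments. They do not show that the principal investigator knows patients before assigning them.

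**Step 4: what the planned analysis would remove.** The Data analyses section says that "treatment conditions (experimental vs. control) will be included as the between-subjects factor and time", with the interaction of the two examined. On the mean scale, the interaction is a difference in change:

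(Iconic after − Iconic baseline) − (Support after − Support baseline).

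Suppose steering made the Iconic arm's scores higher by a constant amount s at every visit. The first bracket becomes (Iconic after + s) − (Iconic baseline + s), and s cancels. Suppose instead that steering put patients with a better prospect of change into one arm, by an amount c. Then c appears only after baseline and stays in the contrast in full. The model therefore removes a stable difference in severity and leaves a difference in prognosis for change. The planned chi-squared and t tests at baseline look at measured characteristics only and would not reveal c.

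**Step 5: size.** The documents give no information on how many patients might be misplaced or by how much their prognosis would differ. Any number would be invented, so none is given.

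**The case against.** The best defence has four parts.

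*Silence is not a defect.* A journal article condenses a protocol, and a concealed list may exist. This stands in part. A reader might infer that allocation is not concealed. The article does not say so, and a sequence withheld from the recruiting clinicians is not ruled out. What remains is that the article names the allocator, and an unreported list would not by itself make that person independent.

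*Others recruit, and allocation may be done in one batch.* Recruitment runs until the sample is reached, patients are grouped by age, and four groups of 18 are formed. This can be read as assigning a cohort that is already enrolled, so there would be no next assignment to foresee. That is a fair reading and it narrows the risk. It does not remove it: whoever assigns a named batch can still place or re-place individuals unless the sequence comes from elsewhere.

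*The analysis may absorb an imbalance.* Step 4 above supports this for a stable difference in severity, so it would be wrong to say that no analysis could help. A difference in prognosis for change is not absorbed.

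*The age grouping.* A reader might also infer that age is a stratification factor wrongly left out of the GEE. The documents do not support this as a fault. Grouping by age may only mean composing therapy groups of similar age. Even if age is a stratum, an age effect that is constant over time cancels from the treatment-by-time contrast in the same way as s, so a main effect for age would change essentially nothing there.

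**Conclusion.** The point holds in a limited form. By the article's own statements the allocator is not independent of the treatments, and no safeguard for concealment is described. Concealment is therefore not assured in a trial where the Iconic Therapy psychologists are unblinded and the primary outcome is self-rated. The conclusion does not depend on any assumption about conduct. It rests on two readings of the text: that the principal investigator named in the Randomisation section is the one named in the Iconic therapy group section, and that the remark about earlier delivery includes that person.

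The documents do not establish that allocation is open, that the principal investigator knows patients before assigning them, or that any bias of a given size will follow. The change is worth making because it removes a plausible route to bias at almost no cost. It is not a reason to regard the trial as invalid.

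**What to change.** Replace the Randomisation sentence with text to this effect:

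> A computer-generated 1:1 allocation list is prepared and held by a colleague who takes no part in recruiting, treating or supervising. Each allocation is released only after eligibility has been confirmed and the baseline BSL-23 has been completed.

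State in the same place whether age is a stratification factor or only a way of composing the therapy groups. If it is a factor, the list is generated within age groups. If the whole cohort is assigned at once, the same rule applies: the named list of eligible patients with complete baselines goes to the holder, who returns the assignments.

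The cost is one list, a short change of text and some coordination by an existing colleague. The principal investigator's supervisory and supporting roles need not change, and neither does the statistical model. If a concealed procedure already exists in the full protocol, one sentence describing it and naming the role of the list holder would settle the point, provided that this role is independent.
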